#### Secondary outcomes

The secondary outcomes include additional clinical and operational metrics, assessing both the effectiveness of the warming method and its broader impact on the ART process:Warming media comparison: evaluating embryo survival, blastocyst re-expansion, and implantation success across different brands.Embryo storage devices: assessing the impact of various storage devices on post-thaw embryo viability and clinical pregnancy rates.Embryo culture media: comparing embryo development, implantation potential, and clinical outcomes using different culture media.

All outcomes will be measured at specific time points relevant to the embryo warming, transfer, and post-transfer processes, including follow-ups to 6–8 weeks for clinical pregnancy and further monitoring for live birth.

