**Methods:**

This is a pragmatic, two-arm, double-blinded randomized controlled trial (RCT) comparing the new direct warming method with the conventional multi-step method. Participants undergoing FET will be randomly assigned to either the direct warming method or the conventional warming protocol. The primary outcomes are the clinical pregnancy rate (CPR), ongoing pregnancy rate (OPR), the live birth rate (LBR), miscarriage rate, and cost-effectiveness. Secondary outcomes include identifying clinical differences among various brands of warming media, embryo storage devices, and embryo culture media through subgroup analyses. A sample size of 578 participants is planned, allowing for a 5% loss to follow-up.

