## Introduction

### Background and rationale {6a}

Infertility affects approximately one in six individuals globally, making assisted reproductive technologies (ARTs) essential for many couples attempting to achieve pregnancy [1]. Among ART procedures, frozen embryo transfer (FET) has become the most frequently performed technique, surpassing 2 million cycles annually since the first live birth achieved via frozen embryo transfer using slow freezing [2, 3]. Vitrification has since emerged as the dominant method for embryo cryopreservation, significantly improving survival rates compared to the earlier slow-freezing method [4]. Although vitrification has replaced slow freezing, the corresponding advancements in embryo warming techniques have not progressed as rapidly.

The process of thawing vitrified embryos requires precise and rapid warming rates, specific thawing solutions, and the expertise of skilled embryologists to ensure optimal survival rates [5]. Conventionally, the multi-step warming process gradually dilutes and removes cytotoxic cryoprotectants, maintaining extracellular osmolality to avoid osmotic shock. However, this method typically requires 15–20 min and incurs significant costs, approximately 5500 HKD per procedure. Not only is this multi-step approach costly, but it also extends the time required to prepare embryos for transfer.

Our research introduces a novel direct warming method that offers a faster, cost-effective alternative. Unlike other ultra-fast warming methods, which utilize sucrose or trehalose in thawing solutions, our approach employs embryo culture mediums without any cryoprotectants [6–8]. This method has demonstrated a 100% survival rate in over 100 donated human blastocysts. The entire warming process is completed in just 1 min, reducing the time required by 90% and lowering costs by 80% [9].

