#### Secondary objective

The secondary objective is to evaluate the impact of technical variations (warming media, storage devices, and culture media) on clinical outcomes between the direct warming method and the conventional multi-step method.

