### Trial design {8}

This is a two-arm, double-blinded, parallel-group, multi-center, randomized controlled trial (RCT) with a superiority framework. The trial will compare the efficacy and safety of the new direct warming method against the conventional multi-step warming method for FET.

Participants will be randomized in a 1:1 allocation ratio into one of two groups:Intervention (arm 1): the new direct warming method.Control (arm 2): standard care using the conventional multi-step warming method.

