## Assignment of interventions: allocation

### Sequence generation {16a}

A stratified randomization approach will be used to ensure balanced distribution of participants across treatment groups based on age, a key factor influencing embryo warming and transfer outcomes. Participants will be stratified into two age groups: ≤35 years and >35 years.

Within each age stratum, participants will be randomly assigned to one of two study groups (conventional warming or direct warming) using a computerized randomization process in sealedenvelope.com. Random numbers will be generated for each participant, and participants will be assigned to the intervention or control group randomly, ensuring even distribution across groups within each age stratum.

In the case of an odd number of participants in any stratum, the remaining participant will be randomly assigned to one of the two groups. This method ensures that participants are randomized within each stratum, achieving a balance in age distribution across the treatment groups.

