However, as a multi-center study, the findings may still be influenced by site-specific variations in clinical practices and patient demographics, which could impact generalizability. While the inclusion of multiple centers enhances the study’s external validity, further large-scale trials in diverse settings will be necessary to confirm broader applicability. Additionally, while miscarriage, pregnancy, and live birth rates are primary outcomes, long-term follow-up on birth outcomes, including potential congenital abnormalities, will be crucial to fully assess the safety of this novel method.

This trial protocol is positioned to provide valuable insights into whether the direct warming method can serve as a more efficient and equally effective alternative to conventional multi-step warming. If successful, it could simplify clinical protocols, reduce operational costs, and challenge the traditional understanding of embryo warming processes in ART.

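### The secondary comparisons across warming-media brands, storage devices and culture media are non-randomised, and the article states two different questions for them

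*Protocol article*

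**What the plan says.** All references are to the protocol article.

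- **What is randomised.** Trial design {8}: "Participants will be randomized in a 1:1 allocation ratio into one of two groups", the two groups being direct and conventional warming. Sequence generation {16a}: "Participants will be stratified into two age groups: ≤35 years and >35 years". No section describes any assignment of brand, device or culture medium, and centre is not a stratification factor.
- **Product comparisons as outcomes.** Secondary outcomes, under {12}: "Warming media comparison: evaluating embryo survival, blastocyst re-expansion, and implantation success across different brands". The next two items compare storage devices with each other and culture media with each other. The Methods paragraph of the abstract agrees: "Secondary outcomes include identifying clinical differences among various brands of warming media, embryo storage devices, and embryo culture media through subgroup analyses".
- **The objective.** Secondary objective, under {7}, is to "evaluate the impact of technical variations (warming media, storage devices, and culture media) on clinical outcomes" between the direct and the conventional method.
- **Subgroups and covariates.** Section {20b} names age, embryo quality and cause of infertility as subgroups. The adjustment lists in {20a} and {20b} name patient and embryo characteristics. Neither names centre, though both are open-ended.
- **What the arms use.** Background and rationale {6a} ties commercial thawing kits to current multi-step practice and says of the new method that "our approach employs embryo culture mediums without any cryoprotectants". Intervention description {11a} has the direct arm use a direct warming medium, followed by culture medium.
- **Sites.** The Discussion accepts that "the findings may still be influenced by site-specific variations in clinical practices and patient demographics", in a remark about generalisability. Sample size {14} says the lead centre could recruit all 578 participants.

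**The concern.** A secondary outcome of a randomised trial is usually taken to carry the protection of randomisation. Here it does not. A difference between two devices compares women whose embryos happened to be stored on one or the other. That can reflect the centre, the period, the patient mix or laboratory habit as easily as the device. The wording is nevertheless causal: the outcomes speak of impact and of identifying differences among brands.

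The article also does not settle which quantity it wants. A difference between products (a main effect) and a difference in the direct-versus-conventional effect between products (effect modification) are separate estimands with different protection. The Secondary outcomes section asks for the first. The Secondary objective can be read as asking for the second. The section on additional analyses names subgroups for neither.

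At stake are published comparisons of commercial products that the design cannot support. The trial's main result is not at stake.

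**Working it through.** **1. The sections side by side**

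| Place | Question asked | Randomised contrast? |
|---|---|---|
| Secondary outcomes {12} | Brand against brand, device against device, medium against medium | No |
| Abstract, Methods | Differences among products, obtained by subgroup analysis | No, as worded |
| Secondary objective {7} | Product factors and the contrast between methods | Yes within a level fixed before allocation; no for the difference between levels |
| Additional analyses {20b} | Age, embryo quality, cause of infertility | The three product factors are not named |

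Storage device is fixed before allocation because the blastocysts are already vitrified. Post-warming culture medium is less secure: it could be chosen after the envelope is opened, by an embryologist who is not blinded ({17a}). Multi-step kit brand has no counterpart in the direct arm.

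**2. Inputs for size**

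The article gives no figure for these comparisons. Its overall numbers follow from 275 × 1.05 = 288.75, rounded to 289 per arm, and 2 × 289 = 578. All rates, product splits and equal centre sizes below are assumptions. Tests are two-sided at 0.05.

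**3. Spurious device difference when the device has no effect**

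Take two equal centres of 289, with pregnancy rates of 40% and 50%.

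- *Device fully tied to centre:* the spurious difference is 50% − 40% = 10 points.
  - SE under the null = √(2 × 0.45 × 0.55/289) = 0.0414.
  - SE under the alternative = √((0.24 + 0.25)/289) = 0.0412.
  - P(p < 0.05) = Φ((0.10 − 1.96 × 0.0414)/0.0412) = 0.68.
  - With centre rates of 40% and 45% it is 0.23; with 35% and 50% it is 0.96.
- *Device partly tied to centre (80% use in one, 20% in the other):*
  - First device: 0.8 × 0.40 + 0.2 × 0.50 = 0.42.
  - Second device: 0.2 × 0.40 + 0.8 × 0.50 = 0.48.
  - The spurious difference is 6 points, and P(p < 0.05) = 0.31.

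Complete overlap of product and centre is therefore not needed for a misleading result.

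**4. Kit brand within the conventional arm**

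At most 289 participants contribute. With two equal brands (144 each), power for 40% against 50% is 0.40. With three equal brands (about 96 each) and rates near 50%, the 95% half-width for a pairwise difference is 1.96 × √(2 × 0.25/96) = 0.141, or 14 points. That figure measures imprecision, not confounding.

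**5. Treatment-by-device interaction**

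Take two equal device levels, so 578/4 = 144.5 per cell, and an average rate of 45%.

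- SE of the difference in effects = √(4 × 0.45 × 0.55/144.5) = 0.0828.
- Power for a 10-point difference in effects = Φ(0.10/0.0828 − 1.96) = 0.23.
- Difference detectable with 80% power = (1.96 + 0.8416) × 0.0828 = 0.232, about 23 points.

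**The case against.** The strongest reply is that the Secondary objective, together with the abstract's reference to subgroup analyses, already permits the sound reading: direct against conventional within each device or medium. That contrast stays randomised where the factor is fixed before allocation. This stands for the objective. It does not rescue the Secondary outcomes section, which plainly compares products with each other.

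Model terms may also sit in an analysis plan that is not shown, and both covariate lists are open-ended. This stands too: the absence of centre from the lists would not be a finding by itself. But a model term cannot decide which of two questions the protocol asks.

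Four stronger readings are tempting and are not supported:

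- *Product cannot be separated from centre.* The article does not say which products any centre uses. Centres may use several, and if the lead centre recruited everyone there would be no between-centre confounding, though product choice would still not be random.
- *Brand will be tested by generalised linear models and chi-square tests without centre.* The sentence in {20a} naming those methods concerns implantation and multiple gestation rates; it does not mention brand, device or medium.
- *The warming-media comparison has no meaning in the direct arm.* That arm does have a warming medium, which may have its own brand and may overlap with the culture-medium factor. Only the multi-step kit is missing.
- *The Discussion warns of brand confounding.* Its remark on site variation concerns generalisability.

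**Conclusion.** The point holds in a limited form. The across-product comparisons are observational, may be confounded by centre or by other determinants of product choice, and are worded as effects. The abstract, the objective, the outcome list and the subgroup section do not agree on the estimand. Multi-step kit brand cannot be a factor common to both arms.

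The size of any bias cannot be known from the article. Under the assumed centre rates of 40% and 50%, it would be 6 points with partial overlap of device and centre and 10 points with complete overlap. The better-protected interaction question has about 23% power for a 10-point difference in effects, so it can only be exploratory.

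Severity is minor: the primary comparison, its sample size and participant safety are untouched.

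**What to change.** Reconcile the abstract, the Secondary objective, the Secondary outcomes and section {20b} on one question:

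1. State the secondary objective as whether the direct-versus-conventional effect differs by storage device and by culture medium. Record both before allocation, the medium as the centre's planned one.
2. Estimate this with a treatment-by-factor interaction in a model that includes centre. Report the treatment effect with its interval within each level, and label the analysis exploratory.
3. Report multi-step kit brand within the conventional arm only.
4. Label any remaining across-product comparison as non-randomised and descriptive.

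One limit should be stated with the results. If a factor proves to coincide with centre, its interaction cannot be told apart from a treatment-by-centre interaction, so a difference in effects should not be attributed to the product.

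The cost is wording in four places, one data item fixed before allocation, a centre term and a more modest secondary claim. The sample size does not change.

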### Participant timeline {13}

See Fig. 1 and Table 1.

**Fig. 1 Fig1:**
[figure not shown]
RCT flowchart

**Table 1 Tab1:** Schedule of the study process

Timepoint	Study period							
	Enrollment	Allocation	Post-allocation					Close-out
	IVF talk	0 week	Embryo transfer	10–14 days	6–8 weeks	20–24 weeks	36–40 weeks	6–8 weeks after birth
Enrollment								
Eligibility screen	X							
Informed consent	X							
Allocation		X						
Interventions								
Administration of different embryo warming methods			X					
Assessments								
Post-thaw embryo assessment			X					
HCG test				X				
Ultrasound of gestation					X			
Phone follow-up						X	X	X

### Sample size {14}

The sample size calculation was based on preliminary data indicating approximately a 5% increase in the live birth rate with the new method compared to conventional warming. With type I error (*α*) set at 0.05 and type II error (*β*) set at 0.2 (80% power), and assuming a clinically significant difference of 20% in the worldwide clinical pregnancy rate, the required sample size per arm is 275, calculated using MedCalc 15.6.1. To account for a 5% loss to follow-up, a total of 578 participants will be enrolled (289 per arm). Given that the total number of participating centers is currently undetermined, the leading center, IVFHK-CUHK, will serve as the core recruitment site. This center can independently recruit at least 578 participants.

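### One sample size (275 per arm, 80% power) is tied to two different effects with no control rate: it cannot be reproduced, and the power is far short for the live-birth effect

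*Protocol article*

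**What the plan says.** Sample size {14} opens by basing the calculation on "preliminary data indicating approximately a 5% increase in the live birth rate with the new method compared to conventional warming". The next sentence sets α at 0.05 and power at 80%, and continues: "assuming a clinically significant difference of 20% in the worldwide clinical pregnancy rate, the required sample size per arm is 275". An allowance for 5% loss takes this to 289 per arm and 578 in total.

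Trial design {8} describes a "randomized controlled trial (RCT) with a superiority framework" with 1:1 allocation. Outcomes {12} lists both clinical pregnancy rate and live birth rate among the primary outcomes.

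The article gives no control-arm rate for either endpoint. It does not say whether the 5% and the 20% are percentage points or relative changes, or whether α is one- or two-sided.

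**The concern.** The two sentences name different endpoints and effects that differ fourfold, yet lead to a single number. A reader cannot tell which effect the 80% power belongs to. The section says that the live-birth increase is the basis, so it invites the belief that the trial has 80% power for it.

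The stakes lie in how a null result would be read. If the preliminary estimate is right and the trial has little power for it, a non-significant live-birth comparison is the expected result and says little. A reader who relies on the stated 80% could take it as informative. The risk is concrete because the Introduction aims to show at least equivalence and the Discussion speaks of comparable outcomes.

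**Working it through.** **Inputs from the article:** α = 0.05, power 80%, 1:1 allocation, superiority, 275 per arm, effects of 5% (live birth) and 20% (clinical pregnancy).

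**Assumed, because not stated:** a two-sided test and control rates of 20–60%.

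**Formulas** (pooled-variance test of two proportions, no continuity correction), with p̄ = (p1 + p2)/2, d = p2 − p1, A = √[2p̄(1 − p̄)] and B = √[p1(1 − p1) + p2(1 − p2)]:

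- n per arm = (1.960·A + 0.842·B)² / d²
- power at n per arm = Φ[(d√n − 1.960·A) / B]

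**Step 1. Can 275 be reproduced?** Only by supplying a control rate. With 20% read as a relative increase from 57.5% to 69.0%: A = 0.6818, B = 0.6770, n = (1.3364 + 0.5697)² / 0.115² = 3.633 / 0.013225 = 274.7, so 275. With a continuity correction the control rate must be near 59%. With one-sided α it must be near 52–53%. None of these rates appears in the article.

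**Step 2. 20% as percentage points.** The largest requirement is at 40% versus 60%: n = (1.3859 + 0.5831)² / 0.20² = 3.877 / 0.04 = 96.9, so 97 (107 with continuity correction). No control rate gives 275, and power at 275 per arm exceeds 99%.

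**Step 3. 20% as a relative increase, other control rates.**

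| Control rate | New-method rate | n per arm for 80% | Power at 275 |
|---|---|---|---|
| 40% | 48% | 604 | 47% |
| 45% | 54% | 484 | 56% |
| 50% | 60% | 388 | 66% |
| 55% | 66% | 309 | 75% |
| 57.5% | 69% | 275 | 80% |
| 60% | 72% | 244 | 85% |

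**Step 4. 5% in live birth as percentage points.** Example, 45% versus 50%: A = 0.7062, B = 0.7053, d√275 = 0.8292. Power = Φ[(0.8292 − 1.3842) / 0.7053] = Φ(−0.787) = 22%. Required n = (1.3842 + 0.5936)² / 0.05² = 3.912 / 0.0025, so 1,565.

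| Control rate | n per arm for 80% | Power at 275 |
|---|---|---|
| 20% | 1,094 | 29% |
| 30% | 1,377 | 24% |
| 40% | 1,534 | 22% |
| 50% | 1,565 | 22% |
| 60% | 1,471 | 23% |

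A one-sided test raises power only to 32–41% over the same control rates. For a 5-point gain, 275 is approached only at a control rate near 2% (269 per arm) or near 93%.

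**Step 5. 5% in live birth as a relative increase.** Power at 275 per arm is 5% at a control rate of 20%, 7% at 40% and 11% at 60%, counting rejections in favour of the new method.

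**Step 6. What 275 per arm detects with 80% power.** Solving the power formula for d gives 10.3 points at a control rate of 20%, 11.4 at 30%, 11.9 at 40–45%, 11.6 at 55% and 11.3 at 60%.

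**The case against.** The strongest defence is that α, power and 275 sit in the same sentence as the 20% clinical-pregnancy difference. The 5% live-birth increase comes before it and may be only background. On that reading the article never claims 80% power for 5 points. The mention of a worldwide rate also points to an outside figure, and the full protocol, which is not shown, may state the baseline.

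Much of this stands. A reader might infer that the 80% power is simply false. The documents do not support that: a relative 20% increase from about 57.5% gives 80%, and an absolute 20 points gives more than 99%. The 22–29% is also conditional on an absolute reading of the 5% and on assumed control rates.

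It does not remove the point. The section itself says the calculation was based on the live-birth increase, so testing 275 against that effect is fair. Leaving the baseline to a fuller document would explain a missing detail. It would not explain naming one effect as the basis and then computing from another effect on another endpoint.

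**Conclusion.** The point holds in two parts.

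- **Live birth:** 80% power does not hold for the effect named as the basis. Power is about 22–29% if the 5% is percentage points and about 5–11% if it is relative (two-sided 0.05, control rates of 20–60%). A true 5-point gain would be missed in roughly 71–78% of such trials.
- **Clinical pregnancy:** 80% power can be neither confirmed nor refuted. It is exceeded on the absolute reading, met on the relative reading only at an unstated control rate near 57.5%, and missed at lower rates.

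The first part does not depend on fine assumptions: no control rate between 20% and 60%, and neither choice of sidedness, brings the power for 5 points near 80%.

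**What to change.** Rewrite Sample size {14} to:

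1. name the one endpoint on which the trial is sized;
2. give the control and intervention rates behind 275, with the source of the control rate;
3. say whether the effect is absolute or relative and whether α is one- or two-sided;
4. remove the 5% live-birth increase as the basis for 275, or reconcile it with the clinical-pregnancy effect;
5. state what 275 evaluable participants per arm deliver: with a two-sided test, 80% power for a difference of about 10–12 percentage points (11.4–11.9 for control rates of 30–55%), and only about 22–29% power for a 5-point live-birth difference.

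This is a correction of text, carried to the registry entry if that repeats the figures. It needs no added recruitment. The cost is a less favourable statement of power for live birth.
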